## Introduction

1

Essential hypertension is a common circulatory system disease, which is affected by both genetic and environmental factors,^[1]^ and accounts for more than 40% of the cardiovascular disease total burden.^[2]^ High salt intake can not only increase blood pressure, but also reduce the efficacy of antihypertensive drugs. And 24-hour urine sodium test is the best way to measure an individual's daily sodium intake.^[3]^ Blood pressure variability (BPV) is a basic characteristic of blood pressure and can reflect the magnitude of blood pressure fluctuations over a period of time. Recent research shows that BPV can better reflect cardiovascular activity than blood pressure levels and is more closely related to target organ damage (TOD) in hypertension.^[4–6]^ Failure to detect and treat essential hypertension early can damage important organs such as the heart, brain, and kidneys, causing diseases such as left ventricular hypertrophy, atherosclerosis, and renal failure.^[7,8]^ Left ventricular hypertrophy (LVH) is an independent cardiovascular risk factor in patients with essential hypertension.^[9,10]^ Intima–media thickness (IMT) is a marker that can be used to assess the severity of atherosclerosis.^[11]^ Serum creatinine, endogenous creatinine clearance rate (Ccr) and 24-hour urine microalbumin (MA) were commonly used indicators of renal function. However, the relationship among high salt load, BPV, and TOD in patients with hypertension is unclear. This study recruited patients with essential hypertension in the Department of Cardiovascular Medicine of Chengdu Fifth People's Hospital. Collect basic patient information, blood pressure measurements, blood specimens, 24-hour urine specimens, and other clinical examination results. Carotid IMT, left ventricular mass index (LVMI), serum creatinine or Ccr, 24-hour urine MA, and other indicators were used to evaluate TOD. To clarify the relationship among high salt intake, BPV, and TOD. To lay a good foundation for early detection of TOD in essential hypertension and related measures.

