##### Exclusion criteria

2.3.1.2

Participants who will meet any of the following will be excluded:

(1)Acute or chronic renal insufficiency: eGFR ≤45 mL/minute(2)Severe cardiovascular disease(3)Exclude patients with malignant tumors, hematological diseases, rheumatic immune system diseases(4)Heart failure (systolic)(5)Take routine dose or overdose of diuretics continuously for 2 weeks (but the fixed compound of RASI + 12.5 mg thiazide diuretics can be included).

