#### Collection and determination of 24 hour urine specimens

2.5.4

Keep a normal diet and avoid strenuous exercise before urine retention. Record the start and end time of urine retention and use a wide-caliber container to collect urine for 24 hours. After mixing, measure and record the total urine volume. The urine sodium, urine potassium, and urine protein were measured in the laboratory of Chengdu Fifth People's Hospital and the 24-hour urine sodium excretion and 24-hour urine MA volume were calculated.

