#### Target organ measurement standard

2.5.5

1.Blood vessels: Detection of carotid IMT: The patient lies on his back and turn the head to the opposite side. The distance between the intimal surface of the common carotid artery bifurcation 1 cm non-plaque and the outside of the median was measured, and the maximum value was taken on both sides. According to the relevant diagnostic criteria in the 2010 Chinese guidelines for the management of hypertension, the carotid intima media thickness >0.9 mm is defined as thickening and the local protrusions protrude from the arterial lumen >0.5 mm or IMT > 1.5 mm is defined as carotid atheromatous plaque.2.Heart: LVMI: Measure the left ventricular end diastolic diameter (LVDd), interventricular septum, and left ventricular posterior wall, measure 3 consecutive cardiac cycles and take the average. According to the Devereux formula, calculate left ventricular mass (LVM) and LVMI: LVM (g) = 0.8 × 10.4 × ([IVST + PWT + LVDd]^3^ − LVDd^3^) + 0.6; LVMI = LVM / body surface area.3.Kidney: Serum creatinine or endogenous Ccr: 24-hour urine A. MA is defined as negative urine routinely detected protein, and urinary albumin excretion rate is 30 to 300 mg/24 hour.

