### Statistical methods

2.7

We will use SPSS 17.0 software for statistical analysis in this study. Normal distribution measurement data was expressed as mean ± SD. One-way analysis of variance was used for comparison of means among multiple groups, and SNK test was used for pairwise comparison. The measurement data of non-normal distribution is expressed as median M (P25–P75). After the natural logarithm is converted to the normal distribution data for analysis, the nonparametric statistical method is used for comparison between groups. Nonparametric test was used to compare data between groups. Correlation analysis used Pearson correlation analysis. Covariance analysis was used to compare the differences in BPV between groups, and multiple stepwise regression analysis was performed on target organ factors related to BPV. *P* < .05 is statistically significant.

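### The only kidney cut-off in the target organ standard is microalbuminuria capped at 300 mg/24 h, so a yes/no use of it would group overt albuminuria with normal excretion

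*Protocol article*

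**What the plan says.** - **Role of the marker.** The Introduction lists the kidney measures among the indicators of target organ damage (TOD): "serum creatinine or Ccr, 24-hour urine MA, and other indicators were used to evaluate TOD". It expands MA as microalbumin: "24-hour urine microalbumin (MA) were commonly used indicators of renal function".
- **Definition.** Section 2.5.5, item 3, opens with "Serum creatinine or endogenous Ccr: 24-hour urine A" and then states "MA is defined as negative urine routinely detected protein, and urinary albumin excretion rate is 30 to 300 mg/24 hour". Serum creatinine and Ccr have no threshold there.
- **Specimen.** Section 2.5.4 says "The urine sodium, urine potassium, and urine protein were measured in the laboratory", and then that "24-hour urine sodium excretion and 24-hour urine MA volume were calculated". The abbreviation MA therefore stands for an amount in 2.5.4 and for a class in 2.5.5.
- **Eligibility.** The only renal exclusion in section 2.3.1.2 is "Acute or chronic renal insufficiency: eGFR ≤45 mL/minute". There is no limit on proteinuria or albumin excretion.
- **Analysis.** Section 2.7 plans comparisons of means or ranks, Pearson correlation and analysis of covariance, and adds that "multiple stepwise regression analysis was performed on target organ factors related to BPV". It does not say whether albumin enters as an amount or as a class.

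**The concern.** A marker of organ damage should move in one direction as damage increases. The MA class does not. It is closed at 300 mg/24 h and also requires a negative routine protein test, so a patient leaves the class by getting worse as well as by being normal. The carotid item in the same section handles this differently: thickening starts above 0.9 mm, and the more severe finding (plaque, including IMT above 1.5 mm) has its own category. The kidney item gives the severe end no category.

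The study aims to relate salt intake and blood pressure variability (BPV) to TOD. If MA yes/no served as a renal marker, the patients with the heaviest albuminuria would join the reference group. Where such patients are more frequent at higher sodium or BPV, the estimated association would tend to be too small.

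A second, smaller point concerns the analyte. The 30–300 band is stated for albumin excretion, but the list of urine assays names protein. Albumin excretion cannot be calculated from total protein.

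**Working it through.** **Step 1. Apply the definition as written.** MA-positive means routine protein negative and albumin between 30 and 300 mg/24 h.

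| Albumin (mg/24 h) | Routine protein | Class under 2.5.5 |
|---|---|---|
| <30 | negative | not MA |
| 30–300 | negative | MA |
| 30–300 | positive | not MA |
| >300 | any | not MA |

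The first and last rows fall on the same side, so the yes/no marker is not monotone in albumin excretion.

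**Step 2. Can such patients be enrolled?** Yes. The renal exclusion acts on eGFR at or below 45 mL/minute. A patient with eGFR above 45 is not excluded on albumin or protein grounds.

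**Step 3. How many?** The document gives no prevalence. With the planned 600 patients and an assumed overt share of 2%, 5% or 10%, the number is 600 × 0.02 = 12, 600 × 0.05 = 30, or 600 × 0.10 = 60.

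**Step 4. Effect on an odds ratio, if a binary marker were used.** The splits below are assumed. Each is normal / MA / overt, in percent, for the highest against the lowest sodium quartile.

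- Split A: 60/28/12 against 80/17/3.
  - Albumin ≥30: (40/60) ÷ (20/80) = 2.67.
  - MA band: (28/72) ÷ (17/83) = 1.90.
- Split B: 68/25/7 against 78/19/3.
  - Albumin ≥30: (32/68) ÷ (22/78) = 1.67.
  - MA band: (25/75) ÷ (19/81) = 1.42.

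**Step 5. When does the band attenuate?** Write n, m and o for the normal, MA and overt shares in one quartile, and let f = [m/(m+o)] × [n/(n+o)]. Then the band odds ratio equals the ≥30 odds ratio times f(high) ÷ f(low).

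- Split A: f(high) = (28/40)(60/72) = 0.583 and f(low) = (17/20)(80/83) = 0.819. The ratio is 0.712, and 2.67 × 0.712 = 1.90.
- Split B: f(high) = (25/32)(68/75) = 0.708 and f(low) = (19/22)(78/81) = 0.832. The ratio is 0.852, and 1.67 × 0.852 = 1.42.

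A positive association is attenuated when f is smaller in the high-exposure group. That is the usual result when overt cases are clearly more common there, but it depends on all three shares.

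**Step 6. Other uses of the kidney data.** As a continuous 24-hour amount, a patient above 300 mg/24 h simply has a high value and the order is kept. Serum creatinine and Ccr do not use the band at all.

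**The case against.** The strongest case against runs as follows. The sentence defines microalbuminuria, a term that means a small amount and so properly has an upper limit. It does not define renal damage. Serum creatinine or Ccr are renal indicators too, and the objective in the Abstract names them without MA. Section 2.5.4 calculates a 24-hour amount. Every method named in section 2.7 is for measurement data or ranks, with no chi-square test, logistic regression or odds ratio. On that reading albumin is analysed as a quantity and the difficulty never appears. Urine protein may also be loose wording for urine albumin, and a condensed article may leave coding detail to fuller documents.

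Much of this stands. A reader might infer that the protocol defines renal damage as the 30–300 band and counts patients with overt proteinuria as undamaged. The document does not support that: it states no binary renal endpoint and no counting rule. A reader might also infer that associations could be reversed. Neither split above shows a reversal. One would need a far more extreme distribution (for example, an assumed 60/10/30 against 80/17/3 gives a band odds ratio of (10/90) ÷ (17/83) = 0.54), and nothing in the document points to it.

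Two things remain. The band is the only kidney cut-off in a section that sets the target organ standard, so anyone who forms a renal yes/no variable from that section must use it. And this is a rule that the article states, with a poor result at the severe end; it is not merely detail left out. Nothing in section 2.7 commits the analysis to the continuous amount.

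**Conclusion.** The point holds in conditional form. As written, the MA class places albumin above 300 mg/24 h, and any positive routine protein, on the same side as normal excretion, and eligibility does not remove such patients. If MA yes/no is used as a marker of renal TOD, its association with sodium or BPV would generally be attenuated, provided overt cases are more common at higher exposure.

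The size cannot be derived from the document. The 12 to 60 affected patients and the falls from 2.67 to 1.90 and from 1.67 to 1.42 rest on assumed distributions and on a binary comparison that section 2.7 does not specify. They only illustrate the mechanism. Analyses of the continuous 24-hour albumin amount, serum creatinine or Ccr are unaffected by the band.

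The mismatch between urine protein in 2.5.4 and albumin excretion in 2.5.5 is probably a matter of wording, but it needs to be reconciled however albuminuria is analysed.

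**What to change.** - **Section 2.5.5, item 3.** Classify raised albuminuria as 24-hour urinary albumin of at least 30 mg regardless of the routine protein result, with ordered categories <30, 30–300 and >300 mg/24 h.
- **Section 2.7.** State that the 24-hour albumin amount, log-transformed, is the main albuminuria variable, and that any categorical analysis uses the ordered classes above.
- **Section 2.5.4.** Name urine albumin as the analyte, so that the measurement matches the excretion rate in 2.5.5. Use MA for either the amount or the class, not both.

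Cost: wording only if albumin is already assayed. Otherwise, at most one additional assay on urine already collected.

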#### Grouping criteria

2.5.6

Twenty-four-hour urinary sodium was used to estimate sodium salt intake. Based on the quartiles of the 24-hour urine sodium, the enrolled population was divided into low sodium group, low-to-medium sodium group, medium-to-high sodium group, and high sodium group.

### Data collection, management, and quality control

2.6

To maintain the quality of this trial, and data management including data collection, validation, and completion will be conducted by the Fifth People's Hospital of Chengdu City, Sichuan Province, China. To ensure that outcome assessments are of a high standard in accordance with the trial protocol, the investigator and the assistants will attend a 6-hour training workshop before the initiation of the trial. The investigator and the assistants will also be provided with a written protocol and standard operating procedure documents. All the data will be checked regularly by clinical trial coordinators. The study subjects were selected in strict accordance with the inclusion and exclusion criteria. Blood pressure measurements in patients with hypertension are performed by trained cardiovascular physicians.

### Statistical methods

2.7

We will use SPSS 17.0 software for statistical analysis in this study. Normal distribution measurement data was expressed as mean ± SD. One-way analysis of variance was used for comparison of means among multiple groups, and SNK test was used for pairwise comparison. The measurement data of non-normal distribution is expressed as median M (P25–P75). After the natural logarithm is converted to the normal distribution data for analysis, the nonparametric statistical method is used for comparison between groups. Nonparametric test was used to compare data between groups. Correlation analysis used Pearson correlation analysis. Covariance analysis was used to compare the differences in BPV between groups, and multiple stepwise regression analysis was performed on target organ factors related to BPV. *P* < .05 is statistically significant.

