**Objective::**

The purpose of this study is to compare 24-hour urine sodium excretion, BPV, carotid intima–media thickness, left ventricular mass index, and serum creatinine or endogenous creatinine clearance rate. To clarify the relationship between high salt load and BPV and TOD in patients with hypertension.

This study is a cross-sectional study. It will recruit 600 patients with essential hypertension in the outpatient and inpatient department of cardiovascular medicine of Chengdu Fifth People's Hospital. Researchers will obtain blood and urine samples with the patient's informed consent. In addition, we will measure patient's blood pressure and target organ-related information.

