### Aim of the study

2.1

The objective of this study is to investigate the relationship among high salt intake, BPV, and TOD in patients with hypertension. Through laboratory inspection, echocardiography, and ambulatory blood pressure monitoring, we could identify risk factors and take steps to reduce the risk of damage to the patient's target organs.

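### The only stated multivariable analysis linking BPV to organ damage is a stepwise regression with an unclear outcome, so weak associations may be left out and retained ones overstated

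*Protocol article*

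**What the plan says.** Section 2.1 sets an explanatory aim: "The objective of this study is to investigate the relationship among high salt intake, BPV, and TOD in patients with hypertension". The abstract gives the design and size: "This study is a cross-sectional study" and "It will recruit 600 patients with essential hypertension". The Introduction lists the organ measures: "Carotid IMT, left ventricular mass index (LVMI), serum creatinine or Ccr, 24-hour urine MA, and other indicators were used to evaluate TOD".

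Section 2.7 names these analyses of association:

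- between-group comparisons of means (ANOVA with SNK) or nonparametric tests;
- "Correlation analysis used Pearson correlation analysis";
- "Covariance analysis was used to compare the differences in BPV between groups";
- "multiple stepwise regression analysis was performed on target organ factors related to BPV".

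The significance rule is P "< .05 is statistically significant". Section 2.5.3 defines BPV by both the SD and the CV in each monitoring period. Section 2.5.6 splits 24-hour urinary sodium into quartile groups. Section 2.7 does not say which variable is the outcome of the stepwise regression, or that sodium or any other variable must stay in it.

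**The concern.** The covariance analysis compares BPV between groups and does not involve organ damage. The correlations are unadjusted. Any adjusted statement about BPV and organ damage therefore rests on the stepwise regression, which has two weaknesses.

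First, its direction is unclear. Taken literally, the organ measures are the explanatory factors and BPV is the outcome. Section 2.1 also speaks of finding risk factors so that organ damage can be reduced, which would make the organ measures the outcomes. The two models answer different questions.

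Second, selection and estimation use the same data. A term stays because its estimate happened to be large enough, and its coefficient, interval and P value are then reported as if the model had been fixed in advance. In an explanatory study the reader would take a dropped term as unrelated and a retained one as independently related, at the size shown. Neither inference is safe for weak associations.

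**Working it through.** **Inputs from the protocol article.** n = 600 (abstract); significance level .05, taken as two-sided; stepwise regression (2.7). No effect size, power or correlation is given, so there is no planned figure to reproduce.

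**Assumptions.** Entry at P < .05 and removal at P > .10; 6 candidates (4 true, 2 noise), or 6 or 12 noise candidates for the null case; pairwise correlation 0, 0.3 or 0.5; standardised effects β from 0.05 to 0.20; residual SD 1; 1,000 simulated studies per setting.

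**Step 1: closed form for uncorrelated candidates.** SE = 1/√600 = 0.0408. Let d = β/SE − 1.96. Then P(kept) ≈ Φ(d), and the mean retained coefficient ≈ β + SE × φ(d)/Φ(d).

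- β = 0.10: d = 2.449 − 1.960 = 0.49. Φ(d) = 0.688, so the term is dropped in 31%. The mean when kept is 0.10 + 0.0408 × 0.354/0.688 = 0.121, which is 21% too large.
- β = 0.20: d = 4.899 − 1.960 = 2.94. Φ(d) = 0.998, so the term is dropped in 0.2%. The mean when kept is 0.200, with no material bias.

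**Step 2: simulation over correlations 0, 0.3 and 0.5.**

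| True β | A given true term dropped | All four true terms kept | Mean coefficient when kept | Coverage of 95% interval when kept, correlation 0 | Same, correlation 0.5 |
|---|---|---|---|---|---|
| 0.05 | 67–78% | 0–0.3% | 0.10–0.14 | 87–90% | 54–60% |
| 0.10 | 31–45% | 0.6–22% | 0.12–0.16 | 96–97% | 83–87% |
| 0.15 | 4–20% | 35–79% | 0.15–0.18 | 97–98% | 93–95% |
| 0.20 | 0–4% | 88–99.5% | 0.20–0.21 | 94–95% | 96–97% |

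At β = 0.10 the retained coefficient is 20–56% too large. The lower end, with uncorrelated candidates, is pure selection and agrees with step 1. The upper end also includes effects that pass from dropped, correlated terms to those kept.

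**Step 3: no true association.** For independent tests, the chance of keeping at least one noise term is 1 − 0.95^6 = 26.5% with 6 candidates and 1 − 0.95^12 = 46.0% with 12. The simulation gave 21–27% and 29–48%.

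**Step 4: the same candidates, all kept.** At β = 0.10, a true term is significant in 66–69% of studies at correlation 0, 54–61% at 0.3 and 42–50% at 0.5. Stepwise retention was 65–69%, 63–68% and 55–63%. Forced entry therefore does not raise power. It reports every coefficient, without selection bias.

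**Step 5: all organ measures in one model for BPV.** Suppose five organ measures each correlate r with BPV and ρ with each other. The joint coefficient of each is r/(1 + 4ρ).

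- r = 0.20, ρ = 0.3: 0.20/2.2 = 0.091.
- r = 0.15, ρ = 0.5: 0.15/3.0 = 0.050.

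In simulation over r = 0.15–0.20 and ρ = 0.3–0.5, each organ is significant on its own in 96–99.9% of studies. In the joint model, stepwise keeps a given organ in 33–64%, and forced entry finds it significant in 15–55%. The loss comes from putting correlated organs in one model, and selection does not add to it.

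**The case against.** **Candidate list.** The list of candidates and covariates may stand in a fuller protocol or analysis plan that is not shown, so its absence is no fault. That is right. But stepwise selection is a stated choice, and a plan consistent with section 2.7 would still select by P value.

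**Direction.** A reader might infer that the model reverses the aim. The documents do not go that far. The aim in 2.1 speaks of a relationship without naming an outcome, the design is cross-sectional, and the regression sentence is loose enough to mean organ measures regressed on their related factors. The direction is ambiguous, not shown to be wrong.

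**Sodium.** A reader might infer that sodium will be dropped. Section 2.7 does not say that it enters this model, and sodium can also be examined through the quartile comparisons, the correlations and the covariance analysis of BPV. What stands is that no stated adjusted analysis of organ damage is sure to contain it.

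**Many BPV indices.** SD and CV, systolic and diastolic, over three periods make 2 × 2 × 3 = 12 possible indices. Nothing says that all enter one model, and 2.5.3 singles out the CV of systolic pressure. Even if all did, dropping stepwise selection would not by itself help. With 12 null indices and 8 covariates, at least one false positive arose in 30% of stepwise runs at inter-index correlation 0.5 and 24% at 0.7, against 30.5% and 23% when the indices were entered one at a time. Only naming one index in advance brings the rate near the nominal 5% (4–8% across runs).

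**Effect size.** With strong associations and few candidates the harm is small. Step 2 confirms this.

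**Conclusion.** The point holds in a limited form. The sole stated multivariable link between BPV and organ damage is selected by P value, has no clear outcome, and guarantees no place to sodium or confounders. For a standardised effect near 0.10, a true term is missing in about a third of studies, or up to 45% when candidates correlate at 0.5. Its coefficient is at least about 20% too large when kept. Interval coverage at that effect falls below nominal when candidates are correlated, but not when they are uncorrelated. At 0.20 with six candidates the distortion is negligible.

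Every size here rests on assumed effects, correlations and entry rules, because the article gives none. It would be wrong to conclude that truly related organs will certainly be lost, or that stepwise selection causes the masking among organs. The omission rates also do not show a loss of power compared with a full model. What selection harms is the reporting: omitted terms have no estimate, and retained ones are biased. The change is worth making before analysis, since it is nearly free.

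**What to change.** In section 2.7, replace the stepwise regression with one pre-specified linear model for each organ measure as outcome: carotid IMT, LVMI, log urinary albumin, and whichever renal function measure is chosen. Each model contains the following terms, all kept whatever their P values:

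- 24-hour sodium as a continuous variable;
- one primary BPV index chosen in advance, for example the 24-hour CV of systolic pressure;
- mean blood pressure of the same period;
- age, sex, BMI and antihypertensive treatment.

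Report every coefficient with its interval. Enter other BPV indices one at a time in place of the primary one, and label these models exploratory or adjust them for multiplicity. Without that, the false-positive gain is lost.

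The cost is wording only. The article already plans to collect these variables (sections 2.5.1 to 2.5.5), and seven terms in 600 patients leave about 86 patients per term (600/7). The drawbacks are that some non-significant terms stay in the model and that power per term is not raised.
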